#### Response assessment

Tumor response versus treatment‑related change is assessed on longitudinal MRI per RANO 2.0[31], which requires a confirmation step to reduce misclassification of early post‑treatment effects. New or increasing enhancement on follow‑up is therefore classified as preliminary progression until a confirmatory MRI at 6–8 weeks determines confirmed PD or confirmed pseudoprogression, with the final status backdated to the preliminary timepoint. If MRI follow‑up remains inconclusive, amino‑acid PET may be used.

Pseudoprogression is defined as an early, transient treatment‑related imaging change that typically occurs within 12 weeks after radiation and stabilizes or improves without a change in therapy.

Radionecrosis is defined as a late, progressive radiation‑induced tissue injury occurring months to years after radiotherapy. Histopathology is the reference standard when resection is performed but is not required for diagnosis. All MRI timepoints are read centrally by an experienced academic neuroradiologist, independent of the treating team and blinded to the sulfasalazine dose level, ensuring consistent, unbiased interpretation across participants.

#### Endpoints

Because GKRS is a focal treatment, duration of response is evaluated using FFLP. FFLP is measured from GKRS to local progression of the trial‑treated lesion, with the date of MRI showing local failure as the event and participants without local failure censored at the last imaging follow‑up. PFS is measured from GKRS to any intracranial progression (either in the trial‑treated lesion or at distant intracranial sites) or death from any cause. The date of MRI demonstrating intracranial progression, or the date of death, constitutes the event; participants are censored at the last follow‑up if neither has occurred. OS is measured from GKRS to death from any cause. Death is the event, and survivors or participants lost to follow‑up are censored at the date of last known follow‑up. This structure ensures non‑overlapping endpoints. FFLP captures local failure only, with distant failure and death censored. PFS captures any intracranial progression or death, with participants alive without progression censored. OS captures death only, with survivors or those lost to follow‑up censored at their last known assessment.

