### Data management and analysis

Study data will be recorded in protocol‑specific case report forms and monitored regularly for completeness, consistency, and accuracy. An independent DMC and steering committee will be appointed to oversee safety and the scientific integrity of the study and ensure adherence to the protocol, respectively.

All datasets will be de‑identified before analysis and stored in secure institutional repositories in accordance with local data‑protection regulations. Statistical analyses will be performed using validated software packages, SPSS and R.

The primary endpoint will be determination of the maximum tolerated dose and the recommended phase II dose of sulfasalazine administered as a radiosensitizer. The number of participants experiencing CTCAE v4.0. grade ≥ 3 adverse events will be summarized within each dose cohort, and formal hypothesis testing will not be required for dose determination.

Secondary endpoints will be summarized using descriptive statistics. Secondary endpoints will have limited statistical power due to small sample size and expected attrition related to disease progression or missed assessments. Time‑to‑event secondary outcomes (FFLP, PFS, OS) will be analyzed using Kaplan-Meier method and Cox models, while longitudinal secondary outcomes (tumor volume, KPS, FACT‑Br, SUVmax, and GSH-edited MRS-levels) will be analyzed using MLMs for repeated measures accommodating incomplete follow‑up under a missing at random assumption.

For tumor volume, KPS, and FACT‑Br, fixed effects will include time and interaction with time, with baseline score, age, and sex as covariates. Both intercept and slope of time will be included in the model as random effect factors. Prespecified pairwise contrasts across time points will use a Šidák adjustment for multiple comparisons. For GSH and SUVmax values, fixed effects will include region (tumor vs. normal‑appearing brain), time relative to baseline, and region by time interactions. .

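### Kaplan-Meier analysis of FFLP with death and distant failure censored overstates the probability of local failure

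*Protocol article*

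**What the plan says.** The Endpoints section measures FFLP from GKRS to local progression of the treated lesion and gives it a specific role: "duration of response is evaluated using FFLP". It states the censoring rule twice, in different terms. First, "participants without local failure censored at the last imaging follow‑up". Later in the same paragraph, "FFLP captures local failure only, with distant failure and death censored".

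For PFS, "The date of MRI demonstrating intracranial progression, or the date of death, constitutes the event", and "participants are censored at the last follow‑up if neither has occurred". Imaging is named in the FFLP rule but not in this one.

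Under Data management and analysis, the three time-to-event outcomes "will be analyzed using Kaplan-Meier method and Cox models". No competing-risk method is named. The same section describes the secondary endpoints as descriptive and of limited power.

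Secondary outcomes schedules clinical follow-up and MRI at the same visits (Day 4, 4 weeks, 12 weeks, then every three months to 12 months). It ends them at consent withdrawal, documented tumor progression or death, without saying whether progression means local or any intracranial progression.

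**The concern.** Death makes local failure impossible, and under the second statement distant failure ends observation for FFLP. Kaplan-Meier treats a censored participant as someone who would go on to fail locally at the same rate as those still followed. The curve therefore describes a setting in which nobody dies or fails elsewhere, and its complement exceeds the proportion of participants who actually have local failure.

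Competing events should be common here. The article cites a median PFS of 6 months and a median OS of 12 months in a 12 Gy series (Justification for prescription dose), and its Limitations call glioblastoma diffuse and GKRS focal. With so few participants the curve is likely to be read more than any Cox estimate, and FFLP is the time-to-event endpoint closest to a local radiosensitizing effect. The error makes local control look worse than it is.

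The two statements of the censoring rule add a second problem. Take a participant with distant failure at month 3 and local failure on MRI at month 9. One statement counts an event at month 9; the other censors at month 3.

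**Working it through.** **Sample size.** Four dose levels of three to six participants give 4 × 3 = 12 and 4 × 6 = 24, which reproduces the article's 12 to 24. The article states no target or event count for FFLP or PFS.

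**FFLP inputs.** Median PFS of 6 months is from Justification for prescription dose. Exponential times and the local share *s* of first failures are assumptions; the article gives no share, so it is varied from 0.4 to 0.9.

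- Total hazard of first failure: h = ln 2 / 6 = 0.1155 per month, so exp(−12h) = 0.25.
- Actual probability of local failure by 12 months (cumulative incidence): s × (1 − 0.25) = 0.75s.
- One minus Kaplan-Meier with competing events censored: 1 − exp(−12sh) = 1 − 0.25^s.

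| Local share s | Cumulative incidence | 1 − KM | Overstatement (points) |
|---|---|---|---|
| 0.4 | 30.0% | 42.6% | 12.6 |
| 0.5 | 37.5% | 50.0% | 12.5 |
| 0.6 | 45.0% | 56.5% | 11.5 |
| 0.7 | 52.5% | 62.1% | 9.6 |
| 0.8 | 60.0% | 67.0% | 7.0 |
| 0.9 | 67.5% | 71.3% | 3.8 |

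At 6 months the same formulas, with exp(−6h) = 0.5, give an overstatement of 1.4 to 4.3 points.

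**Death as the only competing event** (treated lesion still read after distant failure, local hazard unchanged). With local hazard 0.5h and an assumed death hazard d, cumulative incidence is 0.5h / (0.5h + d) × (1 − exp(−12(0.5h + d))). For d = 0.01 and 0.03 per month this gives 47.4% and 42.9%, against 50.0% by 1 − KM: gaps of 2.6 and 7.1 points. Using the whole OS hazard, d = ln 2 / 12 = 0.5h, gives 37.5%, a gap of 12.5 points. But local plus death hazards then add up to h, the entire PFS hazard, and leave none for distant failure. At s = 0.6 they add up to 1.1h, an implied median PFS of 6 / 1.1 = 5.5 months. The 12.5 points is therefore an upper figure.

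**Precision.** Ignoring censoring, the standard error is √(S(1 − S)/n). At S = 0.5 it is 14.4 points for n = 12 and 10.2 for n = 24; at S = 0.25 it is 12.5 and 8.8.

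**PFS.** This was simulated with 20,000 participants, first-event hazard h, an assumed 10% of first events being deaths, and MRI at about 1, 3, 6, 9 and 12 months.

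- Ordinary dropout of 10 to 30% by 12 months: censoring at last follow-up and at last MRI differ by about 0.1 point. At 30% dropout they give 24.9% and 24.8%, against 25.0% without dropout.
- 10, 20 or 30% stop MRI by 12 months but stay in contact (post-progression death hazard assumed ln 2 / 6): censoring at last follow-up gives 26.7, 29.0 and 30.7%, against about 25% with complete imaging. The excess is about 2 to 6 points. Censoring at last MRI gives about 25%.

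**The case against.** The strongest reply is that FFLP is an openly declared cause-specific endpoint. The article says what is censored, offers PFS as the composite, and nowhere says that the complement of the curve will be reported as a probability of local failure. Censoring competing events is the correct way to estimate a cause-specific hazard, so the planned Cox model already delivers that. This stands for the Cox model. It does not rescue the Kaplan-Meier curve, which is also planned and will be read on a probability scale. The stated rationale of non-overlapping endpoints does not help either: local progression is an event in both FFLP and PFS, and death in both PFS and OS.

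Second, censoring at distant failure has some support. Limitations warns that salvage treatment of new lesions may confound later radiological outcomes, and assessments may end at documented progression. So continued reading of the treated lesion is neither free of confounding nor assured by the present schedule. This stands and shapes the fix.

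Third, the size depends on an assumed local share. Study rationale says recurrence is typically local; that is not data on failure after GKRS, but it gives no reason to cap the share at 0.6. At 0.8 to 0.9 the gap is 7 to 4 points. This also stands.

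A reader might infer from the PFS wording that the PFS curve is biased too. The documents do not support that: clinical visits and MRI are scheduled together, so the two possible censoring dates largely coincide, and a difference appears only if participants miss MRI while still in contact. A reader might also infer that FFLP will settle phase II planning. The recommended dose rests on grade 3 or higher toxicity, and FFLP is not listed under Aims of study.

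**Conclusion.** The point holds for the FFLP curve. As planned, one minus Kaplan-Meier overstates the probability of local failure at 12 months by about 4 to 13 points over local shares of 0.9 to 0.4, assuming exponential times and the cited median PFS of 6 months. If the treated lesion is followed past distant failure, the gap depends on how often death comes first and could be smaller. Any further bias from dependence between distant and local failure cannot be quantified from the article.

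The error is similar to or smaller than the sampling error with 12 to 24 participants. It always runs in the same direction, however, and more patients would not remove it. Separately, the FFLP censoring rule does not fix one date for a participant with distant failure.

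The PFS wording is an ambiguity, not a demonstrated bias. The consequence overall is modest: secondary, descriptive endpoints, with no bearing on the MTD.

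**What to change.** 1. Report local failure by the Aalen-Johansen cumulative incidence function, with death as a competing event, beside the cause-specific Cox analysis. If follow-up of the treated lesion stops at distant failure, treat distant failure as competing too.
2. State one FFLP rule for participants with distant failure. Reconcile the two statements in Endpoints with each other and with the end of assessments at documented tumor progression in Secondary outcomes. If reading of the treated lesion continues after distant failure, say so and note possible confounding by salvage treatment.
3. As a minor clarification, state that PFS is censored at the last evaluable MRI.

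Items 1 and 3 are changes of wording and use R, which is already planned. Item 2 is also wording if follow-up stops at distant failure; continuing to read the treated lesion may require scans that the present schedule does not guarantee.

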#### Secondary outcomes

Secondary outcome assessments will include clinical (KPS/FACT-Br) follow‑up and standard MRI (T1‑weighted with and without contrast, T2, and FLAIR) imaging at Day 4, 4 weeks, 12 weeks, and subsequently every three months for up to 12 months or until consent withdrawal, documented tumor progression, or death. Tumor response on MRI will be assessed according to RANO criteria for gliomas [21]. At the 1‑month visit, [¹¹C]methionine PET will be performed and evaluated according to PET Response Assessment in Neuro‑Oncology criteria (PET‑RANO), criteria [22] to differentiate pseudoprogression from true progression. GSH‑edited MRS to assess longitudinal changes in intratumoral and normal‑brain GSH levels will be obtained at Day 3, Day 4, and at 1 month.

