## Limitations

This method has several limitations. As a phase I 3 + 3 dose‑escalation study, the sample size will be small, which limits the precision of safety estimates and reduces the ability to detect rare or delayed adverse events. Although the 3 + 3 design identifies the maximum tolerated dose, it provides limited information about dose response relationships and inter- patient variability. It is also possible that the therapeutic window may be wider than anticipated, such that lower doses could achieve meaningful radiosensitization even if they fall below the recommended dose determined by dose‑limiting toxicity criteria.

Radiation‑induced side effects usually emerge well beyond the traditional 30‑day reporting window used in phase I trials. The protocol partially compensates for this through scheduled MRI surveillance for late changes, documentation of radiation necrosis and surgical interventions when required, quality‑of‑life assessments, and [¹¹C]methionine PET imaging when clinically indicated.

The method relies on advanced neuro‑imaging modalities, including GSH‑edited MRS and [¹¹C]methionine PET, which require specialized equipment and expertise. This may limit reproducibility across centers lacking such resources. Early post‑treatment imaging may also be confounded by transient effects such as edema or pseudoprogression, complicating interpretation of metabolic and structural changes and savage treatments for new lesions may further confound radiological and clinical outcome assessments.

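### FFLP has no rule for resection of the treated lesion before local failure is established, so a resected lesion counts as locally controlled, and its post-operative volume as shrinkage

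*Protocol article*

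**What the plan says.** The Endpoints section defines FFLP from GKRS, "with the date of MRI showing local failure as the event and participants without local failure censored at the last imaging" follow-up. It then sets FFLP apart from PFS and OS: "FFLP captures local failure only, with distant failure and death censored". Resection of the trial-treated lesion appears neither as an event nor as a reason for censoring.

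The article expects such operations. Response assessment, where it defines radionecrosis, states: "Histopathology is the reference standard when resection is performed but is not required for diagnosis". Limitations lists, among the ways late radiation effects are followed, "documentation of radiation necrosis and surgical interventions when required". Neither place links surgery or histology to FFLP.

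Under Secondary outcomes, clinical and MRI follow-up runs for up to "12 months or until consent withdrawal, documented tumor progression, or death". Surgery on the lesion is not a stopping point.

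Data management and analysis says that the longitudinal outcomes, tumor volume among them, "will be analyzed using MLMs for repeated measures accommodating incomplete" follow-up under a missing-at-random assumption. It does not say what happens to volumes measured after the lesion has been removed.

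**The concern.** FFLP is the article's measure of duration of response. It should show how long the irradiated lesion stays controlled by the trial treatment. Once the lesion has been removed, later scans show the result of the operation as well.

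Two routes lead to the gap. One is surgery for radionecrosis with no local failure. The other is surgery after an MRI read as preliminary progression but before the confirmatory MRI at 6 to 8 weeks. In the second case the lesion can no longer be confirmed by MRI as it stood, and the Endpoints section names only an MRI as the event. In both cases the participant is carried forward as a local-control success.

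The direction matters more than usual because the trial tests a radiosensitizer, and the DMC oversight section expects that late radiation effects may be modified by radiosensitization. If the combination led to more necrosis needing surgery, FFLP and the volume curve could look better because of that harm. The results are meant to support a phase II trial.

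**Working it through.** **Plan's own figure.** The only planning figure is enrolment: 4 dose levels × 3 = 12 and 4 × 6 = 24, as stated. The point does not depend on it.

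**Applying the stated rule.** Take a participant resected at month 5 without established local failure.
- Event? No MRI has shown local failure, so no.
- Distant failure or death? No.
- Imaging stopped? No; scans continue at months 6, 9 and 12.
- Result: at risk and event-free until the last post-operative scan, unless a later MRI shows local failure.

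**Size, as an illustration.** Inputs from the article:
- median PFS of 6 months in the 12 Gy cohort (Justification for prescription dose), used as an assumed median time to local failure;
- surgery for necrosis in 13% (16 Gy series) and resection in 23% (20 Gy series), same section;
- MRI at about 1, 3, 6, 9 and 12 months.

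Assumptions of mine: exponential local failure, resection before failure at a constant rate m between months 3 and 9, no deaths. After surgery the local-failure hazard is h times its earlier value, with h from 0 to 1.

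The background's almost-half resection figure is not used. It carries the same reference number as the 20 Gy series with 23%.

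Failure hazard: λ = ln 2 / 6 = 0.1155 per month. True 12-month FFLP without resections: exp(−12λ) = 0.25.

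Proportion resected before failure: r = exp(−3λ) × m/(λ+m) × [1 − exp(−6(λ+m))]. Solving for m gives 0.0481 per month for r = 0.13 and 0.0956 for r = 0.23.

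12-month FFLP under the stated rule = (never resected and failure-free) + (resected and without later local failure).
- First part: 0.25 × exp(−6m) = 0.187 for r = 0.13 and 0.141 for r = 0.23.
- Second part if h = 0: all of r.
- Second part if h = 1: 0.25 × [1 − exp(−6m)] = 0.063 and 0.109.

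| Resected | h = 0 | h = 1 | No resection |
|---|---|---|---|
| 13% | 0.187 + 0.130 = 0.317 | 0.187 + 0.063 = 0.250 | 0.250 |
| 23% | 0.141 + 0.230 = 0.371 | 0.141 + 0.109 = 0.250 | 0.250 |

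A simulation of 200,000 participants on the MRI schedule, analysed by Kaplan-Meier, agrees. As written it gives 31.6%, 27.6% and 25.1% (13% resected; h = 0, 0.5, 1) and 37.0%, 29.9% and 25.2% (23% resected).

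**Alternative rules in the same simulation.** Censoring at the last MRI before surgery gives about 24% (13% resected) and 23% (23% resected). Counting every such resection as an event gives 19% and 14%.

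**Participants involved.** With 12 to 24 enrolled, 13% is 1.6 to 3.1 participants and 23% is 2.8 to 5.5.

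**The case against.** The strongest reply is that rules for intercurrent surgery usually sit in the full protocol or SAP, neither of which is shown, and that the quoted sentence only separates the three endpoints. That would answer a complaint of missing detail. Here, though, the article states an event and a default censoring rule for everyone else, and that rule already gives an answer for a resected lesion. For tumor volume the reply has more force: the article never says that post-operative scans are analysed. That part rests on the default reading, in which a scan that was done is not a missing visit.

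Several limits stand.
- Recurrence is typically at the resection margin, as Study rationale says, so a zero hazard after surgery is the extreme case. With an unchanged hazard there is no bias.
- The 13% and 23% rates come from 16 and 20 Gy series. The 12 Gy cohort reported no radionecrosis.
- Where local failure is confirmed, Response assessment backdates it to the preliminary scan and it is an event. Only resection without established failure falls in the gap.
- The standard error of a 25% proportion is √(0.25 × 0.75 / 24) = 8.8 points at 24 participants and 12.5 at 12, before censoring. The upper-end shifts of 7 and 12 points are therefore of the same order as sampling error.
- Censoring at surgery is not assumption-free. It treats resection as unrelated to failure risk, and on the MRI schedule it falls 1 to 2 points below 25%.

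A reader might also infer more than the documents support:
- **SUVmax and GSH models equally affected.** GSH and scheduled PET end at 1 month, so later surgery hardly touches them.
- **New systemic therapy leaves the same gap.** Patients receiving or planning such therapy during the study are excluded, and no size can be put on unplanned use.
- **Limitations concedes that salvage treatment distorts FFLP.** Its caveat concerns new lesions, which are distant failures and already censored for FFLP.

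**Conclusion.** The point holds for FFLP as defined and, on the default reading, for tumor volume. A lesion resected before local failure is established is counted as controlled until the last post-operative scan. If surgery does not raise the local-failure hazard, the bias is zero or in favour of treatment.

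Under the assumptions above, a true 12-month FFLP of 25% would read as 25% to 32% with 13% resected and 25% to 37% with 23% resected. It would be tempting to conclude that FFLP will be materially inflated in this trial. The documents do not support that: the resection rate at 12 Gy combined with sulfasalazine is unknown, and the effect may be small or nil. FFLP and tumor volume are secondary outcomes with acknowledged limited power. MTD determination and dose escalation are not affected.

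**What to change.** In the Endpoints section, add that resection of the trial-treated lesion without previously established local failure censors FFLP at the last MRI before surgery, or counts as local failure if histology confirms tumor progression. State which date the histology-based event carries. Add a sensitivity analysis that counts every such resection as an event; together with the main analysis it shows how far the result depends on the rule.

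In Data management and analysis, state that volumes of the treated lesion measured after its resection are left out of the tumor-volume model, and that the number of participants affected is reported.

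The cost is a few sentences. Surgical interventions are already to be documented, and histology serves as the reference where resection is done. The downside is slightly fewer scans in the volume model and a possibly less favourable FFLP.
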